## Abstract

**Introduction:**

In the UK, 150 000 people every year experience mid-substance Achilles tendinopathy. Typically patients are offered a range of treatment options such as exercise, electrotherapy, injections and surgery. With large variations in current practice, there is a pressing need to establish which treatments are effective and which are not. This is the protocol for a multi-centre randomised trial of platelet rich plasma (PRP) versus placebo injection for patients with Achilles tendinopathy.

**Methods and analysis:**

Adult patients with mid-substance Achilles tendinopathy for longer than 3 months will be screened. Randomisation will be on a 1:1 basis, stratified by centre and bilateral presentation. Participants will be allocated to either a single PRP injection or placebo injection. A minimum of 240 patients will be recruited into the study; this number will provide 90% power to detect a difference of 12 points in Victorian Institute of Sport Assessment-Achilles score at 6 months. Quality of life, pain and complications data will be collected at baseline, 2-week, 3-month and 6-month post-randomisation. The differences between treatment groups will be assessed on an intention-to-treat basis.

**Ethics, registration and dissemination:**

This trial was funded by Versus Arthritis and commenced on 1 September 2015 (Versus Arthritis 20831). National Research Ethic Committee approved this study on 30 October 2015 (15/WM/0359). It was registered on the International Standard Randomised Controlled Trial Number (ISRCTN) registry with reference number ISRCTN 13254422 on 28 October 2015. The first site opened to recruitment on 27 April 2016 and the trial was in active recruitment at the point of submitting the protocol paper. The results of this trial will be submitted to a peer-reviewed journal and will inform clinical practice with regard to the treatment of Achilles tendinopathy.

Strengths and limitations of this studyBlinding of interventions.UK wide trial across a minimum of 20 centres to optimise external validity.Primary outcome measure is patient-centred.The main limitation is that cost effectiveness analysis was not included.

## Introduction

Tendinopathy in the mid-substance of the Achilles tendon occurs because of the failure of the tendon to mediate its repair and degeneration processes.^1^ The general population has an incidence of 2.35 per 1000 people, equivalent to approximately 150 000 people in the UK every year.^2^ Achilles tendinopathy is characterised by pain and stiffness over the lower portion of the calf (mid-portion of the Achilles) impacting on all weight bearing activities.^3^

Patients are offered a range of non-operative treatment options for mid-substance Achilles tendinopathy including exercise, electrotherapy and injections. Of these platelet rich plasma (PRP) injections have gained national and international interest following guidelines published by the UK National Institute for Health and Care Excellence (NICE) in 2009 (updated 2013)^4^ and international guidance published by the International Olympic Committee 2010.^5^ Both have highlighted PRP injections as a priority area for research, on the basis that they have the potential to reduce morbidity and the need for surgery. With large variations in current practice, there is a pressing need to establish which non-operative treatments are effective.^6–8^

PRP is defined as the plasma fraction of a patient’s own blood (autologous blood) having a platelet concentration above baseline. Platelets contribute to healing through the action of growth factors.^9^ A Cochrane review of injection therapies for Achilles tendinopathy was published in 2015^10^ and identified only two randomised controlled trials (RCTs) evaluating PRP. The first of these was a feasibility RCT for this study that recruited 20 participants at a single site,^3^ and the second was an RCT that investigated the incremental benefit of adding PRP injections to eccentric loading exercises for 54 participants at a single site.^11^ Following this review two further RCTs were published in 2016 and 2017.^12 13^ They evaluated 60 and 24 participants and both were single site and compared PRP and eccentric loading to placebo and eccentric loading. Of these four trials only one^12^ has documented a significant treatment effect of PRP at 6 months (mean Victorian institute of Sport Assessment-Achilles (VISA-A) score 19.6 (SD=4.5) in PRP group and 8.8 (SD=3.3) in placebo group).

Currently available RCT evidence for mid-substance Achilles tendinopathy is limited to studies recruiting at a single site with small sample size (<60 in each study and only 158 participants in total across all studies) that only evaluate the incremental effect of PRP in addition to pre-specified eccentric exercise based programmes. No studies have evaluated the effectiveness of PRP across multiple sites, in an adequately powered trial. There is a pressing need for adequately powered, multi-centre trials in this important clinical area, which this project will address.

## Preparatory feasibility research

Between May 2009 and March 2012, our research group undertook a pilot RCT, funded by the Chartered Society of Physiotherapy, to evaluate the feasibility of a main RCT.^3^ This study used a process evaluation model to determine the feasibility and acceptability of trial procedures. This work was completed in consultation with a patient user panel and was presented at a Versus Arthritis Achilles tendon think tank in April 2013 to further refine the trial question and procedures.

## Research question

In adults with painful mid-substance Achilles tendinopathy lasting longer than 3 months, does a single injection of PRP (intra-tendinous injection with a peppering technique) improve VISA-A scores by a minimum of 12 points when compared with a placebo (subcutaneous injection of a dry needle and no peppering technique) injection at 6-month post-injection?

## Objectives

### Primary objective

To quantify and draw inferences on observed differences in the VISA-A score between the trial treatment groups at 6-month post-randomisation.

### Secondary objectives

To quantify and draw inferences on observed differences in the VISA-A score at 3-month post-randomisation.To identify any differences in health-related quality of life measurement (HRQoL) between trial treatment groups at 3-month and 6-month post-randomisation.To identify any differences in pain measurements between trial treatment groups at 2-week, 3-month and 6-month post-randomisation.To report the complication profile of PRP injections at 2-week, 3-month and 6-month post-randomisation.

## Methods and analysis

### Study design

A single-participant blinded, multi-centre, randomised placebo controlled trial. (online supplementary file 1).

10.1136/bmjopen-2019-034076.supp1Supplementary data

### Sample size

The primary outcome for the study is the VISA-A score^14^; it has a range between 0 and 100, a lower score indicating more symptoms and greater limitation of physical activity and 100 being asymptomatic. The minimum clinically important difference for the VISA-A score is estimated to lie between 10 and 12 points.^11 12^ From our previous feasibility publication,^3^ VISA-A scores were observed to be approximately normally distributed with a SD of 26. If the true difference between the experimental and control treatment group means is 12 points, a sample of 100 patients in each group will be required to reject the null hypothesis (population means of the experimental and control groups are equal) with probability 0.9 (90% power). This equates to an effect size of 0.46, which we would consider to be moderate. The type I error rate (significance level) associated with this test is 5%. Allowing approximately 15% loss to follow-up, this amounts to 240 patients in total.

### Outcome measures

Outcome measures will be collected at baseline (pre-randomisation) by a suitably qualified member of the research team, face to face at the recruiting site. Baseline participant characteristics to be collected include duration of symptoms, side affected (left, right, bilateral), previous treatments for the Achilles tendinopathy, current medications, weight, height, age, gender, ethnicity, smoking and drinking status and employment status. Participants will then be followed up at 2 weeks by telephone direct from Warwick Clinical Trials Unit (WCTU) and 3-month and 6-month post-randomisation by postal questionnaire sent from WCTU or telephone if no postal response is received (online supplementary file 2).

10.1136/bmjopen-2019-034076.supp2Supplementary data

#### Primary

Currently the VISA-A questionnaire is the only patient reported outcome measure developed with supporting validation and reliability evidence, for this common musculoskeletal presentation.^14^ The VISA-A is condition specific and is designed to have greater sensitivity and specificity than general purpose scales in the target population. The VISA-A contains eight questions that cover three domains of pain, function and activity. An asymptomatic person would score 100, the lower the score the greater the disability. It has been shown to have good test-re-test reliability (r=0.93), inter-rater and intra-rater reliability (r=0.90) and construct validity when the mean scores were compared across patient populations with differing ranges of severity, with no evidence of floor or ceiling effects.^15^ These data will be collected at baseline 3 and 6 months after randomisation, where the 6-month score is the primary outcome.

#### Secondary

Euro-Qol 5 Dimensions Score (EQ-5D-5L^16^) is a generic, validated, cross-disciplinary standardised health utility instrument widely used to assess HRQoL. It has two parts, a visual analogue scale (VAS), which measures self-rated health, and a health status instrument, which will be the focus of this study, consisting of a five-level response (no problems, slight problems, moderate problems, severe problems and extreme problems) for five health domains related to daily activities: (i) mobility, (ii) self-care, (iii) usual activities, (iv) pain and discomfort and (v) anxiety and depression. The five dimensions are combined together to provide a 5-digit number that describes the individual’s health state. The 5-digit responses, from the EQ-5D health classifications, are converted into an overall score using a published utility algorithm for the UK population.^17^ It has good test-retest reliability, is simple for participants to use and gives a single preference-based index value for health status that can be used for broader cost-effectiveness comparative purposes.^18^ These data will be collected at baseline, 3 and 6 months after randomisation.

Pain is assessed using a VAS comprising of a horizontal 10 cm line in length, anchored by two verbal descriptors (no pain and worst imaginable pain) to indicate a participant’s pain level on the day on completing the questionnaire.^19^ These data will be collected at baseline 2 weeks, 3 and 6 months after randomisation.

Participants will be asked if they have experienced any complications during follow-up data collection at 2 weeks, 3 and 6 months after randomisation. Complications expected and related to the study treatment that are collected at the specified time points consist of bruising and discomfort at the venesection site, syncopal (fainting) episode associated with venesection or tendon injection, infection, mild discomfort and bleeding at the injection site, swelling, skin discolouration and allergic reaction.

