#### PRP injection procedure

The whole blood will be centrifuged using the study specific Glo PRP system (Glofinn). Each centre will be supplied with the same centrifuge system to facilitate standardisation of the intervention.

Although treatment in the prone position means that the participant will be facing away from the healthcare professional, the syringe will be masked to make sure that the participant cannot see the contents of the syringe. Participants will then have one injection of the prepared platelet layer (approximately 3 mL) injected into the Achilles tendon using a standard ‘peppering’ technique at the site of the tendon pain. This technique involves a single skin portal and then five penetrations of the tendon.

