#### Placebo injection procedure

For the placebo injection, the masked needle will be inserted under the skin, but not into the tendon. The participant will feel the needle but nothing will be injected. There is an active debate pertaining to the treatment effect of needling trauma,^10^ or the trauma of injecting fluid directly into the tendon. Therefore following discussion with the trial steering committee (TSC) and the data monitoring and safety committee (DSMC) a decision was made that a true placebo arm would need to avoid these possible treatment effects. The group consensus was therefore not to administer the placebo injection intratendinously and under the skin only. At the 6 months time point, following completion of all data collection, participants will be asked if they think they know their treatment allocation or not.

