### Blinding

It will not be possible to blind the research or clinical team involved in treatment preparation or delivery due to the nature of the intervention. All participants will be blinded and not know their treatment allocation through masking of the treatment syringe to prevent them from seeing the contents, as well as by being face-down during the injection. Participants in both groups will wait for approximately 30 min (PRP preparation time), and not be in the same room as the centrifuge. If this is not possible the participant will lie in the prone position and the centrifuge will spin without any PRP being prepared.

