### Adverse event management

Adverse events will be listed on case report form for return to the ‘ATM’ office. Serious adverse events (SAEs) will be entered onto the SAE reporting form and reported to the central study team. All SAEs that occur between date of randomisation and the 2-week follow-up point will be followed-up as per protocol until the end of the trial. All SAEs will be reported to the sponsor (University of Warwick), ethics committee and oversight committees.

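### The list that defines collected complications does not name Achilles rupture or tear, and the plan does not say whether such an event would enter the compared complication rate

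*Protocol article*

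**What the plan says.** Under Outcome measures, Secondary, the article begins with an open question: "Participants will be asked if they have experienced any complications during follow-up data collection at 2 weeks, 3 and 6 months after randomisation". The next sentence defines the content: "Complications expected and related to the study treatment that are collected at the specified time points consist of" bruising and discomfort at the venesection site, fainting, and then "infection, mild discomfort and bleeding at the injection site, swelling, skin discolouration and allergic reaction". Rupture, tear and structural damage to the tendon are not in the list.

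The two procedures differ at the tendon. In the PRP arm about 3 mL is injected into it, and "This technique involves a single skin portal and then five penetrations of the tendon". In the placebo arm the needle does not enter the tendon and nothing is injected. The placebo section explains the choice: "There is an active debate pertaining to the treatment effect of needling trauma", and the committees wanted a control free of such effects.

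A second safety route appears under Adverse event management: "Adverse events will be listed on case report form for return to the ‘ATM’ office", and "All SAEs will be reported to the sponsor (University of Warwick), ethics committee and oversight committees". The same section says that SAEs arising from randomisation to the 2-week contact are followed up to the end of the trial.

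Reporting the complication profile of PRP at 2 weeks, 3 months and 6 months is a secondary objective. Statistical methods lists the complication rate at those times among the secondary comparisons and allows Kaplan-Meier plots by complication class.

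**The concern.** A list introduced by a phrase meaning that it is complete, and limited to events already held to be expected and related, fixes what the complication comparison is about. Two consequences follow.

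First, the listed items are poorly matched to the randomised contrast. Venesection and skin puncture happen in both arms, so the items tied to them say little about PRP. Structural tendon damage is the local harm most specific to entering the tendon, and it has no class of its own. The article does treat rupture as a distinct event elsewhere: a prior rupture on the index side is an exclusion criterion.

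Second, defining the outcome by relatedness puts a causal judgement ahead of the randomised comparison that ought to inform it. An unexpected event more frequent in one arm is what a controlled trial is well placed to show, and a list of expected events is poorly placed to show it.

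At stake is how a clean complication table may be read. If a rupture is recorded on another form and not counted, similar complication rates in the two arms would say little about the tendon.

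**Working it through.** **1. Arm size.** Inputs from Sample size: difference 12, SD 26, power 90%, type I error 5% (two-sided assumed, as the article does not say), about 15% loss, 240 in total.

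- n per group = 2 × (1.960 + 1.282)² × 26² / 12² = 98.7, so 99, against 100 stated. Effect size 12/26 = 0.46, as stated. Power at 100 per group is 90.4%.
- 200 / 0.85 = 235.3, so 236 after rounding up to equal arms, against 240 stated.

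The plan's figures reproduce. With 1:1 allocation the PRP arm has 120 randomised and about 100 followed up. These two numbers are used below.

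**2. The routes by which a rupture could be recorded and counted.**

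| Route | Could it record a rupture? | Does the article say it enters the compared rate? |
|---|---|---|
| Open question at 2 weeks, 3 and 6 months | Yes, if the participant volunteers it | No; the next sentence defines what is collected by the list |
| Listed complications | Not named | Yes, on the natural reading |
| Adverse event form | Yes; not limited to the list | No; how and when events are elicited is not stated |
| SAE form | Yes, if serious; all SAEs are reported | No; the 2-week limit concerns which SAEs are followed to the end of the trial |

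So a rupture can be captured, but no sentence links that capture to the complication rate. Outcome measures describes follow-up by telephone at 2 weeks and by post, or telephone if there is no reply, at 3 and 6 months. The article describes no examination after the injection. The wording of the questions therefore carries much of the weight.

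**3. How much one event matters.** The article gives no rupture rate, so the rates below are assumptions.

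- Upper one-sided 95% bound after zero events: 1 − 0.05^(1/n). For n = 120 this is 2.5%; for n = 100 it is 3.0%.
- Chance of at least one event at true rate p: 1 − (1 − p)^n.

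| Assumed rate in the PRP arm | n = 100 | n = 120 |
|---|---|---|
| 0.5% | 39% | 45% |
| 1% | 63% | 70% |
| 2% | 87% | 91% |
| 3% | 95% | 97% |

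The expected count at 1% is 1.0 to 1.2 events. Even with complete capture, zero events would not exclude a rate of 2%. With so few events expected, losing one changes the picture.

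**The case against.** The strongest reply is that the list was never meant to be the whole of safety collection. The sentence before it asks an open question at all three time points, and the list can fairly be read as the expected and related subset only. Adverse event forms are not limited to it, all SAEs are reported with no time window in that sentence, and the monitoring committee sees safety data. Further interventions are monitored at each follow-up, so a treated rupture could surface there. VISA-A and the pain scale would register deterioration of the tendon. This stands: it is wrong to say that participants are never asked, or that collection is closed.

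A reader might also infer that unblinded site staff screen events for relatedness, since "It will not be possible to blind the research or clinical team involved in treatment preparation or delivery". The article does not support that. Follow-up is run by telephone or post from the trials unit, blinded participants answer, and no case-by-case screening of complications by site staff is described. The relatedness problem lies in how the outcome is defined.

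Nor does the article say that rupture is a known harm of PRP. Its remark on needling trauma concerns a possible treatment effect. The case for naming rupture rests on the difference between the procedures. A further inference, that the trial is set up to declare PRP safe, also goes beyond the text: the objective is only to report a profile, and no safety conclusion is planned.

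Finally, this is a condensed article, and the forms and supplementary files are not shown. They may already contain a rupture item or an open field. That limits the point but does not remove it, because the article gives a specific list and words it as complete.

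**Conclusion.** The point holds as one of definition and counting. As written, the outcome is a set of expected and related events without a class for structural tendon damage. The sections on secondary outcomes, adverse event management and statistical methods do not say whether a rupture recorded elsewhere, or one after 2 weeks, is counted. The complication comparison may therefore not reliably detect a tendon-level harm; that it could not detect one is more than the text shows.

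The primary analysis is untouched. The size depends on rates the article does not give: over assumed rates of 0.5% to 2%, the chance of seeing any event in the PRP arm runs from 39% to 91%, depending on rate and follow-up. The conclusion assumes that the forms follow the article's list. It is worth correcting because it affects a stated objective and costs little.

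**What to change.** - In the secondary outcomes, name Achilles rupture or tear, partial or complete, in either treated leg as a solicited item, asked in the same words in both arms at 2 weeks, 3 months and 6 months. Either leg matters because participants with bilateral disease may have a second injection.
- Add an open item for any other event, and word the list as examples of expected events.
- Record judged relatedness in a separate field. Compare all events by arm first, whatever the judgement, and related events second.
- Reconcile the three sections: state which of the complication question, adverse event form and SAE form feed the complication rate, and that events after 2 weeks count to 6 months.

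The cost is a few items on existing forms and call scripts and more non-specific events to code, with no extra visits. If the forms already hold these items, only the article and analysis text need to change.

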### Screening and eligibility

Eligible patients will be identified from foot and ankle clinics by the local principal investigator (PI) and invited to speak to a suitably qualified member of the research team. The research team member will complete the eligibility checklist in conjunction with a suitably qualified member of the clinical team. Screening logs will be collected by the clinical care team in a minimum of 20 National Health Service trusts in the UK to assess the main reasons for patient exclusion as well as the number of patients willing to take part.

Patients will be provided with verbal and written information about the study. Written informed consent will be obtained (online supplementary file 3) by a suitably qualified member of the research team, after allowing sufficient time for the patient to consider their decision and ask questions about the trial.

10.1136/bmjopen-2019-034076.supp3Supplementary data

Patients aged 18 years or over with pain at the mid-substance of the Achilles tendon for longer than 3 months confirmed by ultrasound and/or MRI are eligible for the trial. Patients will be excluded for the following reasons: (i) if there is presence of a systemic conditions (including diabetes, rheumatoid arthritis, peripheral vascular disease), (ii) if they are unable to adhere to trial procedures, are pregnant or actively trying to become pregnant or breastfeeding at the time of randomisation, (iii) if they have had prior Achilles tendon surgery or rupture on the index side, have had previous major tendon or ankle injury or deformity to either lower leg, (iv) if they have had a fracture of a long bone in either lower limb in the previous 6 months, (v) if they have previously been randomised in the study, (vi) if they have previously had PRP treatment into a tendon or have any contraindication to receiving a PRP injection (haemodynamic instability, platelet dysfunction syndrome, active cancer, septicaemia, systemic use of anticoagulant therapy (eg, warfarin, dabigatran, heparin), local infection at site of the procedure). Low dose aspirin use (or equivalent) is not a contraindication to receiving a PRP injection; therefore, these patients will not be excluded from the study.

Patients presenting with bilateral Achilles tendinopathy will be randomised and treated as one unit, that is, the patient will be randomised rather than the tendon. However an index tendon will be identified (this will be the one the patient perceives to be more severe at the point of randomisation).

